## Results

Study one: analysis of the prospective database 

Descriptive statistics will be used to summarize the demographic, situational, outcome, and adverse event data. This will include proportions, means (standard deviations), and medians (interquartile ranges) with associated 95% confidence intervals as appropriate for the variable type. 

Relief of FBAO will be defined as the resolution of choking symptoms with no further intervention (by bystanders or EMS) required. It will be a binary variable coded as "success" or "failure." Survival will be coded as alive or dead. Survival with a favorable neurological outcome will be assessed using the cerebral performance category (CPC), with a favorable outcome being a category of 1 or 2 (good or moderate) [15]. A CPC will be assigned by the researchers after reviewing participant answers about post-FBAO functional abilities. Adverse events (both patient-related and device-related) will be summarized using descriptive statistics.

One of the medical researchers (SO, KV, or CD) will assess the information for each case to ensure appropriate assignment of outcomes. All of these will be second checked by one of the physician investigators (DS or CD) to ensure accuracy and reliability. The bivariable analysis will be performed using either the student’s T (continuous) or Chi-squared test (categorical, Fisher’s exact test if n <5) to measure the association of collected data with these outcomes. In all cases, statistical significance will be defined at the level of p <0.05 for comparative analysis. 

The stratified analysis will look at clinically important subgroups including adult versus pediatric patients, mild versus severe FBAO, patients with neurological and neurocognitive impairment, type of ACD used (e.g., non-invasive versus minimally invasive), and users’ prior training (e.g., first responder/healthcare worker versus first aid trained versus layperson without training). Finally, outcomes will also be stratified by whether individuals received a single FBAO intervention (e.g., only ACDs) or multiple (e.g., back blows followed by ACDs). This is important to note because any resolution of symptoms after multiple interventions is likely due to a synergistic effect as opposed to one intervention being solely responsible.

If data are missing (or the input by the survey respondent is not usable), the proportion of missing data for each variable will be reported, and for any analysis or calculations, the sample size (n) will be clearly identified.

Study two: analysis of the ACD user interviews

The theoretical domains framework (TDF) will be used to guide the exploration of the ACD users' experience and help identify facilitators and barriers to their use [16]. If proven to be successful, the use of ACDs by first aiders will be a novel process. Most basic life support interventions (with the exception of automated external defibrillators) do not require the use of a device to intervene in a lifesaving situation. Therefore, an understanding of what behaviors facilitate or detract from the use of ACDs will complement any implementation strategies in the future by resuscitation councils and organizations.

TDF is a qualitative framework based on psychological behavior change theory and has been validated for use in the health research setting [16]. Many examples of its previous use exist in the literature. Curran et al.* *used TDF to identify barriers to the use of the Canadian CT head rules by emergency medicine practitioners [17]. Another study, by Francis et al.,* *used the same framework to understand the physicians' decision process when ordering blood transfusions [18]. Its applicability to a variety of evaluations is a strength of the framework.

After an initial 10 interviews are conducted, the data to that point will be inductively analyzed. TDF helps researchers understand behaviors by mapping themes that arise from interviews onto 14 key domains. These domains are knowledge, skills, social/professional role and identity; beliefs about capabilities; optimism; beliefs about consequences; reinforcement; intentions; goals; memory, attention and decision processes; environmental context and resources; social influences; emotion; and behavioral regulation. Two independent researchers (CD, SO, and KV) will code themes from interviews into domains of TDF and then compare them for agreement. The coders will be blinded to the type of ACD used by the participant.

Prior work utilizing the theoretical domains framework (TDF) describes a stepwise approach, and interviews will be conducted until thematic saturation has been reached [16,19]. Thematic saturation will be determined by an explicit stopping criteria.

After the initial 10 interviews are conducted, three more interviews will be conducted, analyzed, and the thematic results compared to the original 10. If new themes emerge in the last three, another interview will be conducted. The stopping criteria will be defined as when three consecutive interviews produce no new themes compared to the prior (i.e., interviews 1-11 will be compared to 12-14; then 1-12 to 13-15, and so on until no further novel themes are identified) [20].

To be clear, no new themes will have occurred when no new shared beliefs emerge (i.e., themes that two or more participants describe). Although idiosyncratic beliefs (i.e., themes only described by one participant) will be commented on in the discussion, they will not be used as a stopping criterion for thematic saturation. In the case that there is a disagreement between coders regarding specific themes, there will be a discussion between the two to try to reach consensus first. If consensus cannot be reached, a third coder will review the discrepancy and make a final decision. Agreement between coders will be measured using Cohen’s Kappa.

Data management and privacy

All survey results and interview transcripts will be encrypted and stored on a secure server with two-factor authentication maintained by the University of New South Wales. 

Prospective survey and interview data will be assigned a unique study ID, and the results will be separated from any identifying information specific to the participant. The code linking the unique study ID to the participant identification will be kept on a separate device and stored separately from the data. The code will only be accessible to the chief investigator (AP) and delegate (CD) as needed.

Audio recordings will only contain the participants’ first names, but during the transcription process, they will be replaced with the participant’s assigned unique study ID to de-identify the record. Once transcribed and validated, the audio recordings will be destroyed.

No individual patient or healthcare provider information will be released at any point. The quantitative results will be presented in aggregate form to ensure the confidentiality of the participants. Direct quotations from interviews included in publications will not involve any identifying or case-specific information.

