Research Aim One: To investigate what situational and patient factors are frequently identified, and which are associated with relief of the FBAO and survival in individuals with a FBAO treated with an ACD.

Research Aim Two: To describe the experiences of individuals who have used ACDs in response to a FBAO and identify facilitators and barriers to the use of ACDs compared to traditional interventions.

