## Materials and methods

This is a multi-method, international observational study that will run from July 1st, 2021 to December 31st, 2023. Two research study designs will be used to address the research aims.

Study development

Following the publication of the systematic review on the effectiveness of ACDs in January 2020, the research team met in late 2020 to discuss a strategy for future investigation [13]. A draft protocol was created and underwent several revision cycles until a final version was completed and agreed upon. In early 2021, contact was made with each manufacturer to arrange a meeting where an overview of the proposed study was introduced and discussed. The CEO of each respective company, as well as several members of their administration and/or medical team, were in attendance, along with the research team. Following this, the project protocol was provided to each company to review before confirming their interest in participating. In March 2021, letters of support were signed by the CEOs of both companies, agreeing to participate to the extent that was outlined in the provided protocol, including assistance with the identification and recruitment of participants. The arms-length independence structure of the project, where manufacturers would not have any role in data collection, analysis, and reporting was reaffirmed. The study was then reviewed and approved by the Health Research Ethics Committee of the University of New South Wales (HC210242) on May 25, 2021.

Following ethics approval, a subsequent meeting was coordinated with each company with a similar cohort of representatives as the initial meeting. Here, the protocol was reaffirmed by the research team, and planning for the launch of the prospective component was discussed. A member of the research team was available to answer any questions the manufacturers had regarding the study during this period via email or phone.

Of note, no significant changes to the study protocol were made after the initial meeting with the manufacturers. A pre-print version of the a priori protocol was released on medRxiv while awaiting peer review [14].

Study one: prospective database development and evaluation

Participants and Recruitment Procedure

Participants who meet the following criteria will be eligible for inclusion in the study:

1. Individuals 18 years of age or older, who have used an ACD on a human to attempt to dislodge a FBAO. 

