## Discussion

These two studies will help to improve the quality of evidence on novel ACDs and will help to shape future guidelines. The results will impact the global response to FBAO and have the potential to save lives by improving the clearance rate of FBAO and stopping the progress of a choking person to cardiac arrest. By employing a multi-method design, the study will address the question of the safety and effectiveness of ACDs as well as explore the users' experience to see if the implementation of ACDs is acceptable and feasible.

However, we recognize that the planned study is not without limitations. Most significantly, is the limitation on data collection for this field. The recent systematic review, by Couperet al., presents the available literature on all FBAO interventions, and the results are summarized in Table 2 [6,7].

**Table 2 TAB2:** Summary of evidence supporting current FBAO interventions from ILCOR’s most recent CoSTR. FBAO: foreign body airway obstruction; No.: number; ILCOR: International Liaison Committee on Resuscitation; CoSTR: Consensus on Science with Treatment Recommendations.

Intervention	Outcome	No. of studies and design(s)	No. of patients included
Abdominal thrusts	Relief of FBAO	Six case series	417
	Survival	Two case series	189
Back blows	Relief of FBAO	Three case series	75
	Survival	One case series	13
Chest thrusts/compressions	Relief of FBAO	One case series	28
	Survival	One observational study	138 (Only 35 received the intervention)
Airway clearance devices	Relief of FBAO	One case series	10
	Survival	One case series	10

Often surprising to those unfamiliar with resuscitation literature is the paucity of available evidence on which guidelines are based. Since FBAOs are rare events with the majority cleared before EMS arrival, rigorous research is challenging [6-8]. Due to their novelty and limited availability, even more rare are FBAOs treated with ACDs. This makes the investigation of health records from a health system looking for a cohort of patients treated with ACDs unfeasible at present. As a result, this study plans on using a self-reporting strategy.

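### Survival and CPC 1–2 are measured after any ACD use, and the single-versus-multiple split does not show how much of that survival followed relief by the ACD

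*Protocol article*

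**What the plan says.** All places are in the Protocol article.

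- **Who is included** (Materials and methods, Study one): adults "who have used an ACD on a human to attempt to dislodge a FBAO". An attempt is enough; success is not required.
- **Relief** (Results, Study one): "Relief of FBAO will be defined as the resolution of choking symptoms with no further intervention (by bystanders or EMS) required". It is binary.
- **Survival** (same section): "Survival will be coded as alive or dead". Favourable neurological outcome is CPC, "with a favorable outcome being a category of 1 or 2 (good or moderate"). Neither sentence refers to relief or to the technique that cleared the airway.
- **Testing** (same section): collected variables are tested one at a time against these outcomes.
- **Attribution safeguard** (same section): "outcomes will also be stratified by whether individuals received a single FBAO intervention (e.g., only ACDs) or multiple (e.g., back blows followed by ACDs"). The reason given is that "any resolution of symptoms after multiple interventions is likely due to a synergistic effect as opposed to one intervention being solely responsible".
- **Aim One** (Introduction): factors "associated with relief of the FBAO and survival in individuals with a FBAO treated with an ACD".
- **Data available** (Table 1): details of the FBAO, ACD and CPR interventions, and EMS activation.
- **Use of the results** (Discussion): "the study will address the question of the safety and effectiveness of ACDs". The Discussion also says that the study cannot give an effectiveness percentage and will speak only to whether ACDs could be effective and safe.

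**The concern.** Relief looks at what the ACD achieved, whereas survival and CPC 1–2 look at the whole chain of rescue. Reported as separate percentages, they do not show how many survivors had been relieved by the time ACD use ended and how many were cleared by something applied afterwards.

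The single-versus-multiple split is the only planned analysis that could separate these groups, and it splits on the number of techniques instead of their order. Back blows followed by a successful ACD, and a failed ACD followed by thrusts, bear in opposite directions on what the device can do, yet both fall under multiple.

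Survival is one of the two outcomes named in Aim One and one of the two listed for each technique in Table 2. The Abstract also plans to set the ACD evidence beside data on traditional techniques. A pooled survival figure placed there without a label could be taken for survival following ACD relief.

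**Working it through.** The document states no sample size, event count or survival rate, so there is no figure to reproduce. The check is of definitions, followed by arithmetic on assumed rates.

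**Step 1. Code four sequences by the stated rules** (reading further intervention as intervention after the ACD, and counting EMS clearance as an intervention):

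| Sequence | Relief | Survival | Stratum |
|---|---|---|---|
| A. ACD only, cleared | success | alive | single |
| B. Back blows, then ACD cleared it | success | alive | multiple |
| C. ACD failed, another technique or EMS cleared it | failure | alive | multiple |
| D. ACD only, not cleared, patient died | failure | dead | single |

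B and C share the same survival code and the same stratum. Only relief separates them, and no planned analysis crosses relief with survival or uses order.

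**Step 2. Size of the gap.** Let f be the share in whom the ACD failed and another technique followed, s1 survival if the ACD relieved the obstruction, and s0 survival if it did not. All three are assumptions.

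- Pooled survival = (1 − f)·s1 + f·s0
- Survival with relief = (1 − f)·s1
- Gap = f·s0
- Share of survivors without relief = f·s0 / pooled survival

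With s1 = 0.98:

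| f | s0 | Pooled survival | Survival with relief | Gap | Share of survivors without relief |
|---|---|---|---|---|---|
| 0.05 | 0.5 | 0.956 | 0.931 | 0.025 | 2.6% |
| 0.10 | 0.5 | 0.932 | 0.882 | 0.050 | 5.4% |
| 0.10 | 0.9 | 0.972 | 0.882 | 0.090 | 9.3% |
| 0.20 | 0.5 | 0.884 | 0.784 | 0.100 | 11.3% |
| 0.20 | 0.9 | 0.964 | 0.784 | 0.180 | 18.7% |
| 0.50 | 0.9 | 0.940 | 0.490 | 0.450 | 47.9% |

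Over f from 0.05 to 0.50 and s0 from 0.5 to 0.9, the gap runs from 2.5 to 45 percentage points.

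**Step 3. The limiting case, with relief shown beside it.** If all relieved patients survive and a fraction r of failures is rescued otherwise, survival is s + (1 − s)·r, where s is relief. For an inert device (s = 0) and r = 0.5, 0.8 or 0.9, survival is 50%, 80% or 90%, reported next to 0% relief. For s = 0.5 and r = 0.8, survival is 0.5 + 0.5 × 0.8 = 90%, next to 50% relief.

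**Step 4. Is the ACD-only stratum clean?** A patient rescued by another technique cannot be in it, so the gap of Step 2 is zero there. Membership depends on the outcome, however: a success with the ACD alone stays, and a failure that prompts another technique leaves. Assume that all successes used the ACD alone and that 10% of failures received nothing else.

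- True relief 50%: 0.5 / (0.5 + 0.5 × 0.1) = 0.5 / 0.55 = 91% in the ACD-only stratum.
- True relief 20%: 0.2 / (0.2 + 0.8 × 0.1) = 0.2 / 0.28 = 71%.

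The split takes rescued failures out of one stratum and blends them into the other.

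**The case against.** The other side has a good deal in its favour.

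- **All-treated survival is legitimate.** It matches Aim One, which concerns survival among people treated with an ACD. A reader might infer that the plan miscodes rescued failures or credits their survival to the device. It does neither: no sentence attributes these survivors to the ACD, and the Results section warns against crediting one technique when several were used. This stands.
- **Relief is reported alongside.** An inert device would show about 0% relief, so the high survival in Step 3 would not mislead a reader who sees both figures. The two percentages also bound the joint result. With relief 0.80 and survival 0.924 (f = 0.20, s0 = 0.7), survival with relief must lie between 0.80 + 0.924 − 1 = 0.724 and 0.80. This stands, but a bound is a poor substitute for a count that can be made directly, and it says nothing about order.
- **The Discussion disclaims an effectiveness percentage.** It does, but in answer to the skew of self-reporting. Rescue after ACD failure is a different problem, and the Discussion still intends to speak to the potential of ACDs.
- **Failure followed by another technique may be rare.** The Introduction describes ACDs as marketed for use after traditional techniques fail, and the example in the Results section has the ACD last. Nothing in the document shows how often the reverse order occurs, so the size is open.
- **An extra cross-table is analysis-plan detail.** On its own it would be. But the article itself fixes the stratification meant to handle multiple techniques, and as fixed it pools the two orders.

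It is also tempting to ask for separate tests of survival associations in relieved and non-relieved patients. That should not be done: it conditions on an outcome of treatment, the cells would be sparse, and if nearly all relieved patients survive there is nothing to estimate.

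**Conclusion.** The point holds as a matter of reporting and interpretation; no outcome is miscoded. Survival and CPC 1–2 as defined describe survival after any ACD use. They do not show survival following ACD relief, and the planned stratification does not supply it, because one stratum mixes the two orders and the other is selected on outcome.

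The size cannot be fixed from the document. It depends on how often the ACD fails and is followed by another technique, and on how many of those patients live. On the assumed grid the gap is 2.5 to 45 percentage points, and it would be near zero if that sequence hardly occurs. The ACD-only figures of 91% and 71% rest on the further assumptions in Step 4. None of these numbers predicts the study's results. The inert-device case in particular is an illustration, to be read only with its relief figure beside it.

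**What to change.** In Results, Study one:

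1. Split the multiple-intervention stratum by order: ACD as the last technique, versus ACD followed by another technique or by EMS intervention. The intervention details and EMS activation in Table 1, with the case review already planned, are the source.
2. Cross-tabulate survival and CPC 1–2 by relief status and by this order, descriptively and without added tests.
3. State three things: pooled survival is survival after any ACD use; the ACD-only stratum is selected on outcome; and statements on ACD potential rest on relief and on survival with relief, with no sole-technique attribution where several techniques were used.

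The cost is one further table and a few sentences. Cells become smaller, and the order of techniques comes from lay reports that the Discussion itself regards as open to recall bias, so cases with unclear order should be shown as such. No new survey item is needed if the intervention details record sequence; whether they do should be confirmed.

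### An open list of factors is tested one at a time against three outcomes at unadjusted p<0.05, with Student's t and no exploratory label, so chance and confounded associations are likely

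*Protocol article*

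**What the plan says.** In the protocol article, Aim One (end of the Introduction) asks which situational and patient factors are often seen and "which are associated with relief of the FBAO and survival in individuals with a FBAO treated with an ACD".

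The Results section, under study one, defines three binary outcomes: relief, survival, and survival with a cerebral performance category of 1 or 2. Adverse events are to be described only. The testing plan is bivariable. Continuous factors get Student's t, and for the remaining factors the rule reads "Chi-squared test (categorical, Fisher’s exact test if n <5) to measure the association of collected data with these outcomes". One threshold covers all of these tests: "In all cases, statistical significance will be defined at the level of p <0.05 for comparative analysis".

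The next paragraph plans stratified analyses by age group, severity, neurological or neurocognitive impairment, device type, user training, and single versus multiple interventions. No shortlist of factors, primary outcome, multivariable model or multiplicity rule is stated. The Discussion says that the study cannot give a percentage effectiveness and calls it initial work. It does not say that the factor associations are exploratory.

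**The concern.** The associated factors are what Aim One delivers, and the Discussion expects the two studies to help shape future guidelines. A factor reaches that list if one unadjusted test gives p<0.05. Three things weaken such a list:

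- **Chance.** Many tests share an unadjusted 5% threshold, and nothing tells the reader to treat the p-values as exploratory.
- **Confounding.** Age group, severity, prior impairment and user training may well be linked. A training effect, for instance, could reflect which obstructions trained users attend. A bivariable test cannot separate the two.
- **Test validity.** Failures may be few: the Introduction reports that all ten earlier device cases were successes. With very unequal group sizes the equal-variance t-test depends heavily on the two groups having the same spread.

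**Working it through.** The article gives no sample size, event count or overall error rate to reproduce. Its only figure is the per-test level of 0.05. Everything marked as assumed below is not in the document.

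**Number of tests.** Table 1 lists 4 participant, 4 patient and 9 situational headings: 4 + 4 + 9 = 17. Several headings hold more than one variable. With three outcomes, 17 × 3 = 51 tests.

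**False positives if every test runs at exactly 5%, tests are independent and no factor matters.**
- Three outcomes: 51 × 0.05 = 2.55 expected; chance of at least one 1 − 0.95^51 = 0.927.
- One outcome only: 17 × 0.05 = 0.85 expected; 1 − 0.95^17 = 0.582.

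**Allowing for few failures.** Fisher's test on sparse tables rejects well below 5%. With an assumed 8 failures in 150 and 10 or 20 exposed, its exact size is about 1%. In simulated data with 5% to 10% failures, the rule with n read as a cell count rejects 2.0% to 4.9% of the time.
- At 1% per test: 51 × 0.01 = 0.51 expected; 1 − 0.99^51 = 0.40.
- At 2% per test: 51 × 0.02 = 1.02 expected; 1 − 0.98^51 = 0.64.
- Simulation with nested outcomes, 100 or 200 cases, 10% or 20% failures and death in half of failures (all assumed): 1.3 to 2.5 false positives; 60% to 83% chance of at least one.
- Simulation with 8 failures and 4 to 5 deaths or poor outcomes (assumed): about 0.65 to 0.70 false positives; 31% to 38% chance.

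The realistic range is therefore roughly 30% to 80%. The lower end is sensitive to how common each factor is assumed to be.

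**Student's t.** Assume 8 failures, 142 successes, equal means, and a failure-group SD of s times the other.
- True variance of the difference: s²/8 + 1/142.
- Variance that the pooled test uses, on average: [(7s² + 141)/148] × (1/8 + 1/142).
- The approximate rejection rate is the two-sided normal tail beyond 1.976 (the critical t on 148 degrees of freedom) divided by the square root of true over pooled variance.

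| s | true | pooled | root of ratio | approx. rejection | simulated pooled t |
|---|---|---|---|---|---|
| 0.5 | 0.038 | 0.127 | 0.55 | 0.03% | about 0.05% |
| 1.5 | 0.288 | 0.140 | 1.44 | 16.9% | about 17% |
| 2 | 0.507 | 0.151 | 1.83 | 28.1% | 28% to 29% |

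Welch's test stays at about 5% throughout. The pooled test is also at about 5% when the SDs are equal.

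**Fisher trigger.** The n in the rule is not defined. In a 2×2 table with 8 failures, the two failure cells sum to 8, so the smaller is at most 4, observed or expected. Either cell-count reading therefore sends the table to Fisher.

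**The case against.** The strongest defence is that this is an initial study of rare events. The Discussion disclaims any percentage effectiveness and looks to later, more rigorous work. Unadjusted testing is defensible for generating hypotheses, and missed factors matter too. For a true odds ratio of 5 with 30% exposed and 8 failures, power falls from about 55% at 0.05 to about 9% at 0.05/51. This stands as an argument against mandatory multiplicity control. It does not stand against saying that the p-values are exploratory, and the Discussion's caveat does not cover the associations.

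The planned stratification covers age group, severity, impairment and training, and deserves credit. But it takes each factor singly, so it is not joint adjustment, and any tests within strata would add comparisons under the same threshold.

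On the t-test, the article never says pooled, the variance option could be left to an analysis plan, and few Table 1 factors look continuous. That limits the reach of the point. Still, the named test is by convention the equal-variance one.

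A reader might infer that the Fisher rule inflates error, because the missing-data paragraph uses n for sample size: "for any analysis or calculations, the sample size (n) will be clearly identified". If n in the test rule meant group or total size, chi-squared would be used with 8 failures, and its exact size reaches 7.4% (20 exposed of 150) or 9.0% (10 exposed). But the later sentence concerns reporting, and a trigger of 5 is ordinary shorthand for a cell count. On that reading there is no inflation. What remains is an undefined symbol.

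**Conclusion.** The point holds. The article fixes one-at-a-time tests of an open factor list against three outcomes at an unadjusted 0.05 in all cases. An unseen analysis plan does not explain this away, because the threshold is stated as a rule and not merely left out.

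The size is moderate. At least one chance association is likely under most assumptions: roughly 30% to 80% with few failures, and at most 93% for 51 tests. The 93% needs independence and exact 5% tests, so it cannot be combined with a scenario of 8 failures, where Fisher rejects only about 1% of the time. The document does not support saying that the list will certainly contain false findings. Confounding between factors is plausible but cannot be sized from the document.

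Student's t can err in either direction, and nothing in the article shows which group has the larger spread. The 17% to 29% figures apply only if the small failure group is the more variable one.

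**What to change.** 1. Report each association as an odds ratio (or a mean difference for a continuous factor) with a 95% CI. Label the p-values exploratory and unadjusted for multiplicity. Cost: wording only.
2. Replace Student's t with Welch's t, or with a permutation or rank test. Cost: almost none, since Welch also holds about 5% when the SDs are equal.
3. If the number of failures allows, add one Firth-penalised logistic model for relief with age group, severity and prior neurological impairment, reported as supportive. Cost: wide intervals. With 8 failures, these three terms plus one factor of interest leave 8/4 = 2 failures per coefficient.
4. As a clarification only, state that n <5 in the Fisher rule means an expected cell count below 5.

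False discovery rate control across the factor-by-outcome tests is optional, given the power it would cost with so few events.
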